#### Measurements of the parents and babies

Extensive online self‐administered questionnaires, validated questionnaires, and research notes recorded by the research teams during follow‐up visits will be used to obtain metadata. First, baseline demographics will be comprehensively documented, including the parents' diets, lifestyles, health status, and psychosocial status (Tables 1, 2). In regard to parental diet, parents' early life (0–18 years old) approach to processed foods, current intake of food additives, and dietary preferences are collected at baseline [28]. The parents' prebiotic and probiotic intake is recorded at each follow‐up, while the food frequency questionnaire (FFQ)‐based food additive consumption questionnaire for the parents is collected at baseline, postnatal months 6 and 18. For parental lifestyles, we recorded data related to maternal smoking status, alcohol intake, and physical exercise during the past week at each follow‐up time point. Paternal information was also recorded at baseline and 6 months after childbirth. Psychosocial status is measured with Patient Health Questionnaire‐9 (PHQ‐9) and Edinburgh Postnatal Depression Scale since the third trimester and at 6 months post‐delivery for mothers [29]. Stool types are recorded at each follow‐up by providing the Bristol stool form scale (BSC) with schematic drawings of different levels of stool [30] (Table 2).

Regarding the infants, the health information is recorded at birth, including any antenatal complications, Apgar score (at 1 min and 5 min), any use of assisted ventilation at birth, any severe complications and the treatment, and any special care baby unit or neonatal intensive care unit admission and the length of stay. Postnatal self‐administered health reports are provided by the mother, and disease status changes are collected by pediatric research nurses during follow‐up at months 2, 6, 12, and 18. Additionally, the feeding status and dietary pattern were collected at delivery, months 2, 6, 12, and 18, and the FFQ of infants will also be measured at months 6 and 18. The early childhood behavior will be measured with The Early Childhood Behavior Questionnaire at 2–7 years old [31] (Table 1).

### How to follow‐up and retain subjects in early life microbiome‐related birth cohort?

#### Follow‐up and retention strategies

Comprehensive strategies are employed to retain participants throughout the study. During the antenatal period, mothers can contact the research team for any pregnancy‐related issues, with unscheduled research visits arranged as necessary. Post‐delivery, mothers often have numerous questions regarding breastfeeding and their babies' health; therefore, a dedicated hotline is established to provide professional nursing advice. Additionally, we offer free health checks, including a skin prick test in year two and an eye test in year three. Regular seminars on topics such as healthy diet, autism, and eczema are organized for families. During these seminars, we inquire about the child's eating habits and provide brief on‐site consultations for any noticeable eating problems. Furthermore, children with concerning standard health check results between 1.5 and 3 years old are offered an in‐depth interview for early assessment of behavioral issues. Notably, we also provide a microbial report for all 1‐year‐old infants at the Hong Kong site, allowing parents to arrange a consultation with the research team if necessary.

Figure 2 shows study participant recruitment and follow‐up until 31st March, 2024. At this stage of recruitment, a total of 2805 mother‐baby pairs (Hong Kong: 1989, Foshan: 700, Kunming: 116) were recruited, with a drop rate of 9.5% (267/2805) had withdrawn consent for participation during antenatal period, with the following reasons: (1) Personal reasons (64.4%), (2) Termination of pregnancy (14.2%), (3) Refused or lost further follow‐up (8.2%), (4) Refused to provide specimens (7.9%), and (5) Baby and/or mother's health problems (5.6%). During the postnatal (at any time point from delivery to postnatal year three) period, a total of 363 mother‐baby pairs were withdrawn (15.2% 363/2394). Specifically, we reached a response rate (with sample/questionnaire collected) of (2198/2394, 91.8%) at trimester two, (2267/2394, 94.7%) at trimester three.

### How to get robust clinical and microbiome data post‐collection?

#### Quality control and data management

Extensive online questionnaires for self‐administration and research notes recorded by the research teams during follow‐up visits will be used to obtain metadata, including demographic data, dietary habits, lifestyle, health supplements, health conditions, medications, and psychosocial status for mothers, fathers, and babies. In the two study sites in mainland China, paper questionnaires will be used initially, with clinical teams later entering the data into an encrypted database. Co‐morbid illnesses and medications will be cross‐checked against the hospital management system, which covers 90% of the out‐patient clinic follow‐up for the entire population. (1) Queue Maintenance and Control of Missed Visits: Enrolled families will be scheduled for more than 20 follow‐up visits from delivery to the child's age of 7 years. One week before each scheduled visit, a reminder call will be made. If a family misses a visit, the clinical team will contact the parents to reschedule within the designated time window. If an in‐person follow‐up is impossible, research teams will conduct a phone interview. After each clinic visit, an individual electronic questionnaire link will be sent via email or social media apps, with parents asked to complete the questionnaires within 2 weeks. A reminder message will be sent if the questionnaires are not completed on time. (2) Quality Control and Data Monitoring: SOPs are established for each stage to ensure data quality and integrity, including study teams' on‐site instructions for completing questionnaires and collecting specimens during antenatal and postnatal visits, guidelines for parents on electronic questionnaire completion, first‐stage data checking, data monitoring, and data set compilation. Data will be saved in a secure, password‐protected database managed by the Chinese University of Hong Kong. The questionnaire data and research notes will be downloaded every 3 months for monitoring. Initially, one member of the monitoring team will review the data set for completeness and errors according to the SOP. Any problematic records will be returned to the clinical team, who will contact parents for corrections. If the data are time‐sensitive, extra attention will be required to ensure accuracy. After the first review, another monitoring team member will recheck the data for quality and logical consistency. Any issues will be annotated and returned to the clinical team for further follow‐up. Queried data will be verified against the hospital management system, and telephone calls will be made if necessary. The updated data set will then undergo a final verification by the monitoring team. Each verified data set will be assigned a batch number, and an independent database team member will compile different batches according to the SOP to maintain data alignment.

#### Robust methodology to handle missing data

After the data management and monitoring by the clinical team for those key variables that maintain a missing rate of more than 30%, the complete case analysis will be conducted [32]. For those longitudinal co‐variates (smoking, alcohol drinking, disease, long‐term medication, chronic disease), the Last Observation Carried Forward methods will be applied to replace the missing data [33]. For data that belong to missing completely at random or missing at random, multiple imputation will be used for data imputation for other constant variables (Baseline characteristics including education, working status, incomes, etc.) or anthropometry data (childhood/infancy height, weight, head circumference) with a missing rate of less than 30% [34].

#### The standard operating procedure (SOP) for metagenomic sequence

DNA extractions of stool samples will be carried out using the Qiagen DNeasy PowerSoil Pro Kit protocol (Qiagen, Cat#47016, 250 reactions). All operations will be completed in the biosafety cabinet (BSC). In parallel, positive control (a microbial community standard (ZYMO, Cat#D6300)) and three negative controls (BSC environment negative control, operation extraction negative control, and preservative solution negative control) will be included for each kit as well as each extraction batch. DNA quality will be checked using gel electrophoresis to determine DNA shearing and using a Nanodrop OneC Spectrophotometer to determine DNA quality. Qualified DNA samples will be stored at −80°C for further library construction. Extracted DNA concentrations will be measured using Qubit (ThermoFisher) with the Qubit dsDNA BR Assay Kit (ThermoFisher). Illumina sequencing libraries will be prepared from 1 to 300 ng DNA using the Illumina DNA Prep kit according to the manufacturer's recommended protocol, with reaction volumes scaled accordingly. Additionally, Nuclease‐Free Water (not DEPC‐Treated) (Invitrogen™) will be utilized as one negative control, and ZymoBIOMICS Microbial Community DNA Standard (Catalog #: D6306) will be constructed for one positive control. The library concentration is determined by the Qubit dsDNA HS Assay Kit (ThermoFisher), while the quality of the library is checked by analyzing pooled libraries using the Agilent 2100 Bioanalyzer with a High Sensitivity DNA kit to determine the average fragment size of 600 bp. Libraries will be sequenced on the Illumina Novaseq. 6000 platform with 150 bp paired‐end reads. For sequence depth, a sequencing depth of round 5 gigabase (Gb) per fecal sample is aimed. And it is worth further adjustments based on preliminary data outcomes. For sequencing quality, quality score Q30 is used to assess the quality of sequencing reads [35]. The samples with Q30 (%) higher than the quality threshold that Illumina officials provided (≥85% of bases higher than Q30 at 2 × 150 bp for NovaSeq. 6000 System, https://www.illumina.com/systems/sequencing-platforms/novaseq/specifications.html) will be considered as qualification. To mitigate the risk of longitudinal metagenomic sequencing, which may introduce batch effects, during the metagenomic sequencing phase, we are implementing proactive quality control measures in our wet‐labaratory procedures. Specifically, each batch of DNA extraction and library construction will include both a Positive Technical Control (PTC, consisting of a mock microbial community) and a Negative Control (NTC, a no‐template control). The PTC serves as a benchmark to quantify technical variation across batches, while the NTC is used to monitor potential contamination. This approach provides an empirical measure of batch‐specific technical noise and establishes an objective basis for subsequent computational adjustments. Additionally, to further minimize batch effects across different stages, we will employ computational tools designed to correct for such artifacts. Methods such as conditional quantile regression (ConQuR), negative binomial regression models, or the multivariate integration method will be applied as appropriate to ensure robust and reproducible results [35, 36, 37].

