### How to select the representative study sites?

In MOMMY, we specifically aimed to examine the differences between regional (urban vs. rural) lifestyle and their impacts on the vertical transmission of microbiota. Urban lifestyles have been associated with increased risk for “Western” diseases and the pathogenesis of such diseases related to gut microbiome dysbiosis [18]. However, the effects of urban lifestyle on the early life microbiome remain unknown. Here, we incorporated a well‐established urban location, a recently expanded industrialized population, and a third urban site predominated by rural‐to‐urban populations. Hong Kong (**Study site 1**) is a highly urbanized and densely populated metropolitan city. Foshan (**Study site 2**) is an equally important part of the Greater Bay Area as a national base for advanced manufacturing and Guangdong's key production hub. In recent years, it has upgraded and transformed its manufacturing industry, ranking first in industrial technology transformation investments in Guangdong Province for four consecutive years. Foshan was also one of the first in national demonstration base for agricultural industrialization [https://www.bayarea.gov.hk/en/about/foshan.html]. In contrast, Yunnan is a large province in China consisting of both urban and rural residents. Kunming (**Study site 3**), the provincial capital of Yunnan, is an urban city with a multi‐ethnic and diverse population originating from rural districts spanning Yunnan [19, 20, 21]. Furthermore, these cohorts are stratified by their economics, with high incomes in Study Site 1 and lower incomes in Study Sites 2 & 3 (Figure 1B).

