### How to place MOMMY in the world map of global early life microbiome research?

The MOMMY will include three stages (Figure 3A). The study was approved by the Institutional Review Board of all participating centers. The Human Genetic Resources Administrative Permit application is being prepared and will be secured before any genetic analysis. Stage I (September 2019‐September 2024), which was an initial phase to manage infrastructure, recruit subjects and build an integrative microbiome analysis platform to standardize reproducible body‐wide microbiome SOPs for sampling, data generation, and computational methods for microbiome analysis and epidemiology interpretation. Despite the challenges of the COVID‐19 pandemic, we were able to recruit around 2800 families, resulting in 2500 births in Hong Kong, Foshan, and Kunming. Amongst these families, over 130,000 biological samples were collected, including stool, maternal/cord blood (for buffy coat, serum, and plasma [EDTA]), placenta, urine, vaginal swab, buccal swabs, breastmilk, nasal swabs, hair, and nail) and >30,000 web‐based clinical metadata that included dietary habits and lifestyle data based on validated questionnaires from parents and their infants at multiple time points in the antenatal, delivery and postnatal period. Apart from the clinical progress, we also performed large‐scale in‐house metagenomic sequencing on stool samples. Infants were followed up to 3 years of age with over 80% retention rate in three sites, especially the Hong Kong site (Figure 2). Interestingly, five nationalities (Chinese, Canadian, Korean, American, Malaysian, and 99.9% were Chinese) and 13 ethnicities (Han, Hui, Huang, Mang, Tujia, Buyi, She, Miao, Dong, Man, Yao, Amei, Yue) are in MOMMY to date (Table 3). Although the sample size of ethnic minorities is limited, we may conduct pilot studies to explore the uniqueness of lifestyle, epigenetics, and microbiome in these specific populations and may expand sub‐studies according to the relevant research aims.

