Including following options: rheumatoid arthritis, systemic lupus erythematosus, psoriasis, or others.

^7^
Including following options: asthma, atopic dermatits/eczema, food allergy, allergic rhinitis, or others.

^8^
Including following options: coronary atery disease or others.

^9^
Including following options: hepatitis B carrier, other hepatitis, fatty liver, and others.

^10^
Including following options: glomeronephritis, diabetic nephropathy, or others.

^11^
Including following options: polycystic ovarian syndrome, or others.

^12^
Including following options: gestational diabetes, prediabetes (slightly high blood sugar, but not diabetes), type 1 diabetes, type 2 diabetes and age of onset).

During Stage II (September 2024–September 2029), the 2800 families recruited during the first stage will be further followed up till 7 years old of children. Specifically, MOMMY will develop the management algorithm and tools to define the healthy early life microbiome in the first 1000 days in the Chinese population, identify predictors for childhood allergy atopy march and neurodevelopmental disorder (NDD) diseases, and offer early intervention and prevention. Besides, it will be an implementation stage to expand up to 20,000 family pairs (mother, father, and their newborns) and collect the world's largest cohort of 100,000 maternal, paternal, and fetal samples through collaboration with hospitals and partners in mainland China, such as the northern or central cities of China.

In Stage III (September 2029–September 2034), the large‐scale families recruited during Stage II will follow up and further investigate the childhood disease. In this phase, we will focus on children in the critical developmental age of 5 to 7 years. This age group is particularly vulnerable to various adverse conditions and physiological states, such as NDDs and obesity, which require targeted interventions to promote their well‐being and development. By targeting a subgroup of infants, we aim to create effective microbiome interventions that address the adverse conditions faced by children. MOMMY will scale up and establish an Alliance of Early Life Microbiome to foster interdisciplinary efforts to reach new horizons.

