### MOMMY inception cohort: Research novelty and projections

In the MOMMY inception cohort, biosamples including stool, breastmilk, vaginal swab, skin swab, maternal and cord blood have been prospectively collected from 1200 Hong Kong families (mothers, fathers, and offsprings) from pregnancy until the birth of infants followed up to first years of age as of the end of March 2024. In total, >10,000 stool samples from the MOMMY inception cohort families (mother, father, and their infants who reached 1 year old) have been performed in metagenomic sequence (Figure 3B). Leveraging the standardized reproducible body‐wide microbiome sampling SOP, data generation, and computational methods for microbiome analysis and epidemiology interpretation, we will be able to build this platform to integrate microbiome analysis to dissect host microbiome interactions, epigenetics changes, and microbiome trajectories in health and early life.

To maximize the scientific yield, we organized the MOMMY inception cohort into two layers of projects (Figure 4)**:**
*

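### The stools reported as sequenced come from Hong Kong families and no cross-site mixing or bridging samples are stated, so regional contrasts risk batch confounding that computational correction alone may not resolve

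*Protocol article*

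**What the plan says.** The section on the metagenomic sequencing SOP sets out two layers of protection against batch effects. The first is a mock-community positive control and a negative control in each extraction and library batch, to measure technical variation and detect contamination. The second is that "to further minimize batch effects across different stages, we will employ computational tools designed to correct for such artifacts". The tools named are ConQuR, negative binomial regression and a multivariate integration method, chosen as the case requires. The section says nothing about how samples from different sites, stages or visits are allocated to batches, and mentions no stool samples re-run in later batches.

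The section on the inception cohort says that samples "have been prospectively collected from 1200 Hong Kong families (mothers, fathers, and offsprings) from pregnancy until the birth of infants", and reports sequencing of more than "10,000 stool samples from the MOMMY inception cohort families".

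Under site selection, "we specifically aimed to examine the differences between regional" lifestyles is given as a specific aim, with Hong Kong, Foshan and Kunming as the sites. Stage I recruited about 2800 families, "resulting in 2500 births in Hong Kong, Foshan, and Kunming". The section on follow-up and retention gives recruitment to 31 March 2024 as "Hong Kong: 1989, Foshan: 700, Kunming: 116". The Stage II paragraph adds new families "through collaboration with hospitals and partners in mainland China, such as the northern or central cities of China" and continues follow-up of the Stage I families until the children are 7.

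**The concern.** A regression-type correction learns the batch shift by comparing like samples across batches. Where a batch holds one site only, the batch shift and the site difference enter the data as a sum. The correction then either removes part of the real site difference or leaves batch noise in it, and the output does not show which has happened.

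The sequencing reported so far is described as Hong Kong only, and any further regions can enter only in later batches. The exposed results are therefore the regional contrast, which is a stated aim, and any comparison between stages. Analyses confined to the Hong Kong inception cohort involve no site contrast and are not affected in this way. The timing matters because balance can be built into future batches cheaply, but is expensive to restore once Stage II sequencing is done.

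**Working it through.** The article gives no sample size or precision for the site contrast, so there is no figure of its own to reproduce. The check asks what a batch-adjusted site contrast can learn under different batch layouts.

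**Inputs from the article**
- Early sequenced stools: taken as 10,000, all Hong Kong (inception cohort section, which says more than 10,000).
- Recruitment: 1989 + 700 + 116 = 2805. Hong Kong is 1989/2805 = 70.9%; the mainland sites are (700 + 116)/2805 = 816/2805 = 29.1%.

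**Assumptions, because the article does not give these**
- All early stools form one block of batches and later stools another, with n later stools (10,000 as base case; 4,000 and 50,000 as range).
- A share h of the later stools is from Hong Kong and of comparable visit type; h runs from 0 to 71%, the recruitment share.
- Stools are treated as independent with equal variance σ².

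**Model:** outcome = intercept + β × (later batch) + δ × (non-Hong Kong site).

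*No Hong Kong stools in later batches (h = 0).* The design has two distinct rows for three parameters, so its rank is 2 of 3. The later mean minus the early mean estimates β + δ, and neither term can be recovered separately from the study samples.

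*Some Hong Kong stools in later batches.* Let a = h × n (later, Hong Kong) and b = n − a (later, other sites).
- Adjusted for batch: Var(δ) = σ²(1/a + 1/b). The 10,000 early stools do not appear in this formula.
- Ignoring batch: Var(δ) = σ²(1/(10,000 + a) + 1/b).
- The variance inflation is the ratio of the two.

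Worked case, n = 10,000 and h = 10%: a = 1,000 and b = 9,000. Adjusted: 1/1,000 + 1/9,000 = 0.0011111. Unadjusted: 1/11,000 + 1/9,000 = 0.0002020. Ratio = 5.5.

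| Hong Kong share of later stools | Variance inflation, n = 10,000 |
|---|---|
| 0% | not estimable |
| 1% | 50.5 |
| 5% | 10.5 |
| 10% | 5.5 |
| 25% | 2.5 |
| 50% | 1.5 |
| 71% | 1.2 |

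For n = 4,000 to 50,000 the inflation is 71.7 to 17.5 at h = 1%, and 7.4 to 2.5 at h = 10%.

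**Is mixing feasible?** Yes. The mainland sites already hold 816 pairs. Hong Kong has recruited 1989 pairs against 1200 inception families, a difference of 789 before withdrawals.

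**The case against.** Several points against the concern are sound.

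- *Batch composition is not stated.* The article does not say that mainland stools are unsequenced or were run separately, and the sequencing-progress figure is not available. A reader might infer that batch is already largely aliased with site and stage, and that no correction can separate them. The documents do not support that: exact collinearity needs a Hong Kong share of zero in later batches, which is stated nowhere.
- *The three sites of the regional aim all recruited in Stage I.* Only further regions are tied to later stages by design.
- *Hong Kong follow-up continues through Stage II*, so Hong Kong stools can enter later batches. This stands in part. Those from the inception families will come from older children and from mothers after pregnancy, whereas transmission is assessed with late-pregnancy maternal stool. They are weak comparators for new pregnancy and infant samples.
- *The mock community measures technical variation independently of site.* This also stands in part. It covers extraction and library steps for the taxa it contains. It does not pass through participant collection, preservative, transport or storage, and says nothing direct about taxa it lacks.
- *The regional aim concerns transmission, measured within mother-infant pairs*, and no bias in that rate has been shown. That is correct. The argument applies directly to abundance contrasts; for strain transmission rates the size and direction of any batch effect are unknown.
- *Batch layout may sit in a laboratory document that is not shown.* It may. The point here is not the missing detail. The article sets out its strategy for batch effects across stages and expects robust results from it, and that expectation depends on overlap the text does not secure.

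**Conclusion.** The concern holds in a limited form. The sequencing reported so far is described as Hong Kong only, the regional contrast is an aim, and the stated safeguards are controls plus computational correction, with no cross-site mixing or bridging. To the extent that early batches hold only Hong Kong stools, they contribute almost nothing to a batch-adjusted site contrast. If later batches hold no comparable Hong Kong stools, the site effect is not identifiable from the study samples.

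The actual degree of aliasing cannot be fixed from the article. In the simple model above, the cost runs from negligible (inflation 1.2 at a 71% Hong Kong share) through 5.5 at 10% to non-estimability at 0%. These figures assume two blocks of batches, independent stools and comparable visits. Repeated samples within families, and older children standing in for infants, would reduce the useful overlap further. This is an inexpensive improvement that protects a stated aim; it does not show that existing results are wrong.

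**What to change.** 1. From now on, balance or randomise samples across sites, by visit type, within each extraction, library and sequencing batch. Use not-yet-sequenced Hong Kong samples alongside Foshan, Kunming and any new regions.
2. Re-run some tens of banked Hong Kong stool aliquots from matching visits, such as late pregnancy and infancy, as bridging samples spread over the later batches. The number is a judgement, since the article gives no technical variance; the spread seen in the mock controls could inform it. This presumes that suitable aliquots remain, and longer storage of the bridges should be noted as a limitation.
3. Keep the mock and negative controls as planned.
4. Base regional and stage contrasts on mixed or bridged batches, and show corrected and uncorrected results side by side.
5. State the site composition of the batches already run, so that readers can judge the overlap.

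The cost is a layout rule, a modest amount of extra sequencing and somewhat later reporting of site contrasts, because mainland samples must wait to be run together with Hong Kong ones.
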